## Abstract

**Background:**

During the COVID-19 lockdown period in the United Kingdom that began on March 23, 2020, more than a quarter of a million people with cancer reported worsening mental health. Help to Overcome Problems Effectively (Hope) is a self-management program for people with cancer, designed to provide support for distress, unmet needs, and poor psychological health. In light of social distancing during the COVID-19 pandemic, digital delivery of the Hope Programme has become ever more vital for people with cancer. Previous pre-post studies of the digital Hope Programme have found reduced anxiety and depression and improved well-being for people with cancer. However, evaluation of this evidence has been limited by the lack of a control group in these previous studies.

**Objective:**

We now present a protocol for a feasibility randomized controlled trial of the digital Hope Programme for people with cancer during the COVID-19 pandemic. Primary outcomes will be recruitment, dropout, and adherence rates, and estimations of sample and effect size. To detect signals of efficacy, secondary outcomes will be participant mental health and well-being.

**Methods:**

Participants will be recruited by Macmillan Cancer Support (MCS) through their social media networks. The study will employ a feasibility wait-list randomized controlled trial (RCT) design, with people with cancer being randomized to join the digital Hope Programme immediately (intervention group [IG]) or join a 6-week waiting list (wait-list control group [WLCG]) with a 1:1 allocation ratio. Participants will complete digital measures of depression, anxiety, mental well-being, and confidence in managing their own health. Online questionnaires will be administered preprogram and 6 weeks postprogram.

**Results:**

All people who had requested access to the Hope Programme from MCS (N=61) will be invited to participate in the trial. Baseline data collection commenced in April 2020, and the Hope Programme began for the IG in May 2020 and for the WLCG in June 2020. Postprogram data collection was completed by the end of August 2020.

**Conclusions:**

This feasibility study will provide data to inform the design of a future definitive trial. Wider-scale provision of the digital Hope Programme has potential to improve the lives of thousands of people with cancer and reduce the burden on health care providers during these unprecedented times.

**Trial Registration:**

ISRCTN Registry ISRCTN79623250; http://www.isrctn.com/ISRCTN79623250

**International Registered Report Identifier (IRRID):**

DERR1-10.2196/24264

## Introduction

### Background and Rationale

The COVID-19 pandemic has created additional challenges for people with cancer, both in terms of physical and mental health. Many people with cancer are considered at increased risk of serious complications if they were to contract the COVID-19 virus [1]. People with cancer have reported concerns about the further risks to their health from COVID-19, increased anxiety relating to potential cancellation or reduction in treatments and advice from oncology and other medical teams, and significant anxiety and fears of contracting COVID-19 as restrictions in lockdown arrangements are eased [2]. The pandemic has negatively impacted both the cancer health systems and the people using them. Overall, 1 in 5 (20%) people with cancer in the United Kingdom report that they will not feel safe enough to leave their home until an effective treatment or vaccine for COVID-19 becomes widely available [3].

People with cancer are already known to face challenges following primary treatment, including fatigue, pain, sexual problems, issues with cognitive functioning, depression, anxiety, social isolation, and financial issues [4-8]. A significant number of patients with cancer experience long-term negative impacts on their psychological well-being and mental health, including hypervigilance, anxiety, posttraumatic stress, and depression [9-14]; indeed, 2 years postdiagnosis, up to 20% met criteria for major depression and up to 40% met criteria for an anxiety disorder [13,14]. Many of these difficulties are experienced long-term, after regular contact with health care professionals has ceased, which leads to many patients feeling vulnerable and unsupported [5,7,8]. A recent review published before the COVID-19 pandemic came to light highlights the need for urgent research into the longer-term effects of cancer treatment on mental health, as increasing numbers of people live with and beyond cancer [15]. During lockdown, one in four (28%) people with cancer have experienced depression, anxiety, and stress, and one in seven (14%) people with cancer experienced further decline in their physical health (eg, sleep problems, extreme tiredness, and pain) [3]. Macmillan Cancer Support (MCS) have called for the UK government to ensure that holistic physical and mental health support for people with cancer is not forgotten as a result of the COVID-19 pandemic [3].

In the United Kingdom, the National Health Service (NHS) “Long Term Plan” of 2019 [16] places great emphasis on the need for holistic, person-centered care, with greater digital delivery for both NHS services overall and specifically those relating to living well with and beyond cancer. A holistic approach is timely, as recent research shows complex interrelationships between fatigue, fear of cancer recurrence, anxiety, and depression in people with cancer [17,18]. In response to the COVID-19 pandemic, there has also been a rapid and essential growth in the provision of health care digitally, to allow remote care [19,20]. A recent review and meta-analysis showed that digital psychoeducational interventions are effective in significantly reducing depression and fatigue in people with cancer [21]. Many people, including older adults, have become more motivated to use, accepting of, and familiar with digital technologies for health care and social connection [22]. This is essential to meet the needs of people with cancer, as traditional face-to-face support is cancelled and social isolation increases, particularly as in the United Kingdom and many other countries, people with cancer are being advised by the government to isolate or “shield” from others for prolonged periods [23,24].

Around 10 years ago, in response to the shortage of available, tailored self-management support for people with cancer, we codesigned a program together with people with cancer, clinicians, and other experts. The result was a group-based self-management program called the Help to Overcome Problems Effectively Program, known as the “Hope Programme,” for survivors of all types of cancer [25,26], which was originally delivered in-person. The Hope Programme recognizes the common challenges and unmet needs across all types of cancer including fatigue and psychological distress [4-14]. The Hope Programme differs from many other cancer self-management programs due to its roots in positive psychology [27-29] and its focus on hope and gratitude [30] to improve well-being and coping. It has been delivered in person to groups of survivors of all cancers and specifically for survivors of breast cancer, and participants have reported feeling more confident and hopeful and less alone [25,26]. The face-to-face version has been adapted for digital delivery, and initial pretest-posttest evaluation suggested potential effects on anxiety, depression, and positive well-being, with positive user evaluations [31]. A feasibility randomized controlled trial (RCT) study is the next step in the testing of this digital intervention and is required to assess whether participants consent to being randomized, and to test the feasibility of operating a wait-list control group. Owing to COVID-19, in-person service provision has largely been cancelled and this presents the opportunity to conduct the feasibility RCT of the digital intervention. This protocol has been prepared in accordance with SPIRIT (Standard Protocol Items: Recommendations for Interventional Trials) guidelines for clinical trials [32].

### Objectives

The aim of this study is to test the feasibility of a digitally delivered self-management program for people with cancer. This will inform the design of a definitive RCT. Additionally, preliminary assessment of the impact of the Hope Programme, via secondary outcomes, will be used to assess signals of efficacy in a trial context.

The planned primary outcomes (trail feasibility objectives) of the study are to investigate the following:

Recruitment rates for participation and for randomizationRetention and follow-up rates as the participants move through the trialAdherence rates to study procedures, intervention attendance, and engagementSample size and effect size estimation for a definitive trialProgression criteria for a definitive trial

The secondary outcomes are the following:

Measures of depression, anxiety, confidence to self-manage cancer (patient activation), and mental well-being, as indicated by scores on validated measures

### Trial Design

This study will employ a feasibility, randomized wait-list control group design, to explore the feasibility of a trial of the digital Hope Programme for people with cancer. The intervention is a 6-week digital self-management program. Quantitative monitoring of participant progress through the online program will be undertaken. Participants will be asked to complete standardized measures of depression, anxiety, mental well-being, and confidence in managing their cancer.

## Methods

### Study Settings

This is a digital study and the recruitment, intervention, and data collection will be carried out entirely online. Participants are referred by MCS.

### Eligibility Criteria

Inclusion criteria for the feasibility RCT are the following:

Diagnosis of any type of cancer, at any stageAdult (≥18 years)Located in the United KingdomAccess to the internet and a device that will allow them to engage with the interventionFluent in English to be able to engage with all the material in the interventionNot recruited via the NHS

### Intervention

The Hope Programme will be delivered by Hope for the Community (H4C) Community Interest Company, which is a research social enterprise spinout company from Coventry University [33]. Full details of the digital Hope Programme content are described in Multimedia Appendix 1. All Hope Programme modules have the same structure and format, consisting of quizzes, videos, educational content, activities with homework suggestions, and a module review page. The digital Hope Programme is adapted from the in-person Hope Programme, which was developed in conjunction with cancer survivors and MCS staff. The Hope Programme content comprises text, images, downloadable documents, and links to external websites. The content delivered is configured into interactive activities (eg, quizzes, self-monitoring tools, diaries) that can be used by participants to learn and consolidate the program content. The Hope Programme uses forums and messaging facilities that act as a conduit for communication between participants and facilitators. The Hope Programme is asynchronous, and content is released at set times over the 6 weeks. The Hope Programme is moderated by trained peer facilitators.

### Primary Outcome Measures (Trial Feasibility Objectives)

#### Recruitment Rates

Recruitment rates for participation and randomization will be collected through Qualtrics. All eligible participants identified by MCS will be sent a link to the Qualtrics study survey, so we will calculate recruitment rates from those providing consent and/or completing baseline questionnaires.

#### Retention and Follow-up Rates

Follow-up will be online. Participants who become lost to follow-up will be identified through Qualtrics as those not completing postprogram questionnaires. It is possible that these participants may still complete some or all of the Hope Programme, and so participant retention can be identified separately through engagement with the Hope platform (see below). Participants who explicitly request to be withdrawn from the study will be categorized accordingly, but we will not contact participants to obtain reasons for not completing questionnaires.

#### Adherence Rates

The Hope platform collects user engagement data such as login frequency and duration, which assists the moderators with participant engagement and experience. Participants also have the option of receiving system-generated automatic nudge reminders sent to their email address. We will analyze this user engagement data to generate usage patterns and provide an overview of session attendance and participant engagement.

#### Sample Size and Effect Size Estimation

To inform sample size estimation for a future definitive trial, we will calculate the standard deviations of the continuous secondary outcomes pertaining to depression, anxiety, mental well-being, and participant confidence in managing their cancer. To estimate potential effect sizes for a primary outcome in a future definitive trial (namely, change in scores on key secondary outcome measures from preprogram to postprogram), we will calculate the difference between the mean difference preprogram and postprogram for the intervention and control groups and divide by the pooled standard deviation at baseline [34].

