### Assignment of Intervention

#### Allocation Sequence Generation

The participants will be randomly assigned to the IG or WLCG using a 1:1 allocation ratio. Randomization and the allocation sequence will be generated automatically on completion of the online consent form and baseline questionnaires, using the randomization function in Qualtrics Survey Software (Qualtrics). The research team will be unable to influence any aspect of the randomization procedure.

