#### Statistical Methods

Quantitative data will be analyzed descriptively. Measures of mean and variance, including confidence intervals and standard deviations, and number and percent for categorical variables, will be used to describe the full range of data at baseline and postprogram. An intention-to-treat analysis will be incorporated, where missing data will be rectified using the last observation carried forward [42]. Between-group inferential comparisons will not be performed as the study was not designed to be powered for this analysis, in concordance with the CONSORT (Consolidated Standards of Reporting Trials) extension for pilot and feasibility trials [43]. All analyses will be performed using IBM SPSS Statistics 26.

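### The planned effect size and SDs do not determine N for a change-score or baseline-adjusted definitive trial; a baseline-adjusted estimate, the SD of change and the T0-T1 correlation should be added

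*Protocol article*

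**What the plan says.** Sample size and effect size estimation for a definitive trial is one of the listed primary outcomes (Objectives). The section Sample Size and Effect Size Estimation gives the method in two sentences.

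- **On SDs:** "To inform sample size estimation for a future definitive trial, we will calculate the standard deviations of the continuous secondary outcomes". No time point is attached. Statistical Methods adds that means, SDs and confidence intervals "will be used to describe the full range of data at baseline and postprogram".
- **On effect size:** the future primary outcome is identified as "change in scores on key secondary outcome measures from preprogram to postprogram". For it, "we will calculate the difference between the mean difference preprogram and postprogram for the intervention and control groups", and the authors then "divide by the pooled standard deviation at baseline".

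Neither section names the SD of change, the T0-T1 correlation or a baseline-adjusted difference. Statistical Methods also states that "missing data will be rectified using the last observation carried forward", and it rules out inferential comparisons between groups. No alpha, power, target effect or analysis model for the definitive trial is given.

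**The concern.** The numerator of the effect size is on the change scale and the denominator is on the raw-score scale. Such a ratio describes the effect, but it cannot be used as it stands in a two-sample formula for the outcome the protocol names. The variance of a change score depends on how strongly T0 and T1 are correlated, and so does the residual variance after adjusting for T0. SDs at both time points do not supply that correlation.

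There is a second, smaller issue. The difference in mean change is unadjusted. With 20 to 30 people per arm, the arms can differ noticeably at T0 by chance, and part of that difference passes into the estimate through regression to the mean.

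At stake is how useful a primary output of this study will be. Whoever designs the definitive trial would have an effect size and SDs, but not the quantity that turns them into an N.

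**Working it through.** **No figure to reproduce.** The protocol calls its n=40 arbitrary and calculates no N, power or effect size. What follows is illustrative.

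**Inputs from the protocol.** Participants are "randomly assigned to the IG or WLCG using a 1:1 allocation ratio". Each arm has 20 (half of n=40, Sample Size) to about 30 (Participant Timeline). The effect d is in baseline-SD units, as the protocol defines it.

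**Assumptions.** d=0.40, two-sided alpha 0.05, power 80%, r from 0.3 to 0.7, and equal SDs at T0 and T1 unless stated.

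**Step 1: d used directly.** n per arm = 2(1.96+0.842)²/0.40² = 98.1, so 99.

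**Step 2: the variance each analysis needs, in units of the baseline variance.**
- Change score: 1+1-2r = 2(1-r)
- ANCOVA (T1 on arm plus T0): 1-r²

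These factors are also the ratios of required N to the N in Step 1. They do not depend on d, alpha or power.

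| r | Change: ratio | Change: n per arm | Change: power with 99 per arm | ANCOVA: ratio | ANCOVA: n per arm | ANCOVA: power with 99 per arm |
|---|---|---|---|---|---|---|
| 0.3 | 1.40 | 138 | 66% | 0.91 | 90 | 84% |
| 0.5 | 1.00 | 99 | 80% | 0.75 | 74 | 90% |
| 0.7 | 0.60 | 59 | 95% | 0.51 | 51 | 98% |

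For example, 98.1 × 1.40 = 137.3, so 138; and 98.1 × 0.51 = 50.03, so 51.

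**Step 3: unequal SDs.** Let the T1 SD be k times the T0 SD. The change ratio is 1+k²-2rk and the ANCOVA ratio is k²(1-r²). At k=1.2 and r=0.3, 0.5, 0.7, the change ratios are 1.72, 1.24, 0.76 and the ANCOVA ratios are 1.31, 1.08, 0.73. So direct use of d can err in either direction for both analyses.

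**Step 4: chance imbalance.** The SE of the baseline difference in SD units is √(2/n): 0.32 at n=20 and 0.26 at n=30. With equal SDs, the unadjusted change difference carries (1-r) times the observed imbalance. At r=0.5, a one-SE imbalance moves it by 0.16 or 0.13 SD, which is about 40% or 32% of an effect of 0.40.

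**Step 5: can the missing quantities be obtained?** Yes. T0 questionnaires are completed before randomization (Participant Timeline; Allocation Sequence Generation), and responses are linked across time points by a unique ID (Data Management; Confidentiality).

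**Step 6: effect of LOCF.** For anyone without T1 data, LOCF sets T1 equal to T0. That places the pair on the line of identity, tends to raise r, and pulls the mean change towards zero. An r or SD of change taken from LOCF-filled data would therefore tend to look too favourable for sizing.

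**The case against.** Several points on the other side are sound.

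- **The effect size is legitimate.** Dividing a difference in mean change by the pooled baseline SD is a recognised standardisation for a controlled pre-post design, and the baseline SD is untouched by treatment. The denominator is not a mistake. This stands.
- **The protocol does not rest sample size on the baseline SD alone.** A reader might infer this by running the two sentences together. The baseline SD is fixed only as the effect-size denominator. The sentence on SDs gives no time point, and Statistical Methods reports SDs at both. This stands, but it does not close the gap, because two SDs without r still do not give the SD of change.
- **No definitive trial has been sized.** A reader might conclude that it would be mis-sized. That needs a step the protocol never takes: entering d unconverted into a two-sample formula. The 99 per arm above is an illustration, not the protocol's number. This stands.
- **Absolute statements fail.** That direct use of d suits change scores only at r=0.5, or never suits ANCOVA, holds only with equal SDs (and, for ANCOVA, nonzero r). At k=1.2 the ANCOVA ratio passes through 1 near r=0.55.
- **The unadjusted difference is unbiased over repeated randomization.** This is true. The imbalance point is conditional on the allocation that actually occurs, which matters for a single small trial.
- **A cautious r shrinks the saving.** With 40 pairs and an observed r of 0.6, the Fisher 95% lower limit is about 0.35. Then 1-r² is about 0.87, and 98.1 per arm becomes about 86, against 63 at r=0.6 itself.
- **A condensed article may leave such outputs to a fuller document, and linked data allow r to be computed later.** This has weight as to what is merely unlisted. The unadjusted estimator, however, is a choice the article states for a primary objective, and a better one is available from the same data.

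**Conclusion.** The point holds in a limited form. For a future outcome that it defines as change, the protocol fixes an unadjusted estimator standardised by the baseline SD. The outputs it names do not determine N for either a change-score or a baseline-adjusted trial.

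If d were used directly, equal SDs and r between 0.3 and 0.7 would give a required N from 1.4 to 0.6 times that figure for change scores, and from 0.91 to 0.51 times for ANCOVA. The range of r is assumed, the direction of error depends on it, and for change scores the error vanishes at r=0.5. Unequal SDs shift all of these ratios.

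The documents do not support saying that the definitive trial will be mis-sized or that the effect-size definition is wrong. This is a worthwhile improvement at almost no cost.

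**What to change.** In Sample Size and Effect Size Estimation, with a matching line in Statistical Methods:

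1. For each scale, also estimate the T1 between-arm difference by ANCOVA (T1 on arm plus T0) with a 95% CI. Present it as estimation without a hypothesis test, which respects the exclusion of inferential comparisons and fits the confidence intervals already promised.
2. Report the SD at T0, the SD at T1, the SD of change, and the T0-T1 correlation with its CI. Compute these on observed T0-T1 pairs, not on LOCF-filled data.
3. State that definitive sizing will use the T1 SD × √(1-r²), with a cautious r such as one towards the lower confidence limit.
4. Keep the change standardised by the baseline SD, labelled as a descriptive effect size.

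The cost is one paragraph of wording and a few lines of output from data already collected and linked. No extra participants or measurements are needed.

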#### Progression Criteria

We will collate the data from all participants in this feasibility RCT to inform progression to a definitive trial, based on the following criteria:

Recruitment rate >70% of eligible participants consentedQuestionnaire completion rate >70% of participants completing T1 questionnairesProgram completion rate >50% of participants attending all 6 Hope Programme sessions

### Secondary Outcome Measures

We will administer a sociodemographic and health questionnaire at baseline only, requesting the following personal information from participants: gender, age, ethnicity, marital status, highest level of education, employment and occupation, and some details about their cancer diagnosis and any other medical conditions.

Participants will complete a set of validated questionnaires preprogram and postprogram, to give an indication of changes in depression, anxiety, mental well-being, and confidence to self-manage their cancer across the intervention and control groups. These questionnaires are detailed below.

The Patient Health Questionnaire (PHQ-9) [35] is a 9-item measure that assesses the frequency of depression symptoms (eg, “over the past two weeks, how often have you been bothered by any of the following problems … i) little interest or pleasure in doing things; ii) feeling down, depressed or hopeless; iii) poor appetite or overeating”). Responses to each of the 9 items range from 0 to 3 (0=not at all, 1=several days, 2=more than half the days, 3=nearly every day), leading to a summed score between 0-27, with higher scores indicating greater severity of depression. Scores of ≥10 are presumed to be above the clinical range, and so scores of ≥10 are classed as “cases” of depression. Recovery rates are calculated as those patients who score ≥10 (cases) prior to treatment and <10 posttreatment.

The Generalized Anxiety Disorder scale (GAD-7) [36] is a 7-item scale measuring symptoms of generalized anxiety disorder (eg, “Over the past two weeks, how often have you been bothered by the following problems … i) feeling nervous, anxious or on edge; ii) trouble relaxing; iii) becoming easily annoyed or irritable”). Responses to all 7 items range from 0 to 3 (0=not at all, 1=several days, 2=more than half the days, 3=nearly every day), providing a total score of 0-21, with higher scores indicating greater anxiety. Scores of ≥8 are classed as “cases” of generalized anxiety disorder. Recovery rates are calculated as those patients who score ≥8 (cases) prior to treatment and <8 posttreatment.

The Warwick Edinburgh Mental Wellbeing Scale (WEMWBS) [37] is a scale of 14 positively worded feelings and thoughts, used to assess mental well-being within the adult population. The scale includes measures of positive affect, satisfying interpersonal relationships, and positive functioning (eg, “Below are some statements about feelings and thoughts. Please tick the box that best describes your experience of each over the last two weeks … i) I’ve been feeling optimistic about the future; ii) I’ve been thinking clearly; iii) I’ve been feeling loved”). Participants rate each of the 14 items on a scale of 1 to 5 (1=none of the time, 2=rarely, 3=some of the time, 4=often, 5=all of the time), providing a total positive mental well-being score ranging from 14-70, with higher scores representing greater positive mental well-being. A change of ≥3 is seen as a clinically “meaningful” change [38].

The Patient Activation Measure (PAM) [39] is a validated, licensed tool that has been extensively tested with reviewed findings from a large number of studies. It helps to measure the spectrum of knowledge, skills, and confidence in patients and captures the extent to which people feel engaged and confident in taking care of their condition.

Individuals are asked to complete a short survey and based on their responses, they receive a PAM score (0-100). The resulting score places the individual at one of four levels of activation, each of which reveals insight into a range of health-related characteristics, including behaviors and outcomes. The 4 levels of activation are the following:

Level 1: Individuals tend to be passive and feel overwhelmed by managing their own health. They may not understand their role in the care process.

Level 2: Individuals may lack the knowledge and confidence to manage their health.

Level 3: Individuals appear to be taking action but may still lack the confidence and skill to support their behaviors.

Level 4: Individuals have adopted many of the behaviors needed to support their health but may not be able to maintain them in the face of life stressors.

